### Indicator measurement for the dashboard

Evaluation of healthcare providers’ quality performance is commonly done using a combination of structure, process, and outcome indicators (Table 1) [33, 34]. Our dashboard follows that approach.

**Table 1 Tab1:** Quality of care indicators included in the dashboard

Quality indicators	Type	Definition
Center volume	Structure	The total number of patients treated with EVT in each individual hospital
Number of transferred patients	Structure	Whether patient transferred from another hospital to an EVT hospital
Door-to-needle time	Process	Time from arrival at the emergency department of EVT hospital to IVT initiation
Door-to-groin time	Process	Time from arrival at the emergency department of EVT hospital to groin puncture
eTICI	Outcome	Thrombolysis in cerebral infarction scale to assess intracranial reperfusion, ranging from 0 (no reperfusion) to 3 (full reperfusion)
NIHSS at 24 h	Outcome	The neurological deficit ranged between 0 (normal function) and 42 (completely impaired)
mRS at 3 months	Outcome	Functional outcome score of mRS evaluated 3 months after EVT treatment ranged between 0 (no symptom) and 6 (death)

*eTICI* extended thrombolysis in cerebral infarction, *NIHSS* National Institute of Health Stroke Scale, *mRS* modified Rankin Scale, *EVT* endovascular thrombectomy, *IVT* intravenous thrombolytics

Structure indicators are the total number of patients treated with EVT in each hospital (henceforth referred to as “center volume”), the number of direct (i.e., non-transferred) and transferred stroke patients from other hospitals, and completeness of data.

Process indicators are time from arrival at the emergency department of the intervention hospital to start of the intravenous thrombolytics (IVT) administration (door-to-needle time) for non-transferred patients and time from arrival at the emergency department of the intervention hospital to initiation of EVT (door-to-groin time) for all patients. In case a patient has an ischemic stroke while already admitted to the hospital, then the arrival time is defined as the time the neurologist first assessed the patient. We stratified the indicators by whether patients are transferred or non-transferred from another hospital.

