### Study outcomes

The primary outcome is door-to-groin time. Secondary outcomes are door-to-needle time, eTICI score, NIHSS at 24 h, and mRS at 3 months (Table 1). These outcomes are collected for every individual patient (Table 1).

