### Power calculation

The power calculation was based on mean differences in door-to-groin time as a primary outcome. We used a parametric power estimation methodology for stepped wedge designs put forward by Hemming and Girling [39] in the Stata function stepped wedge, derived from Hussy and Hughes [40]. We assumed 13 EVT centers were randomized in four clusters per time step (three clusters of three hospitals and one cluster of four hospitals) that treated an average of 30 patients per center per time period of 3 months [21]. We used a mean door-to-groin time of 77 min (standard deviation 47 min) and *ICC* 0.37, both obtained from the MR CLEAN Registry data [21, 24]. Assuming a significance level of 5%, this would result in 88% power to detect a clinically relevant reduction of door-to-groin time of 10 min.

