### Statistical methods

The effect of the intervention on the primary and secondary outcomes will be assessed by comparing median/percentage outcomes between control and intervention cluster periods and also in the time trends of intervention cluster periods using a non-parametric Kruskal-Wallis test and Pearson’s chi-square statistic, respectively.

Generalized linear mixed modeling at the individual patient level will be used for analyzing the effect of the performance feedback intervention on the primary outcome (door-to-groin time). This will allow us to appropriately account for the different observation cluster periods (both control and intervention) and the hierarchical structure of the data [40]. The model will contain fixed effects for intervention (yes/no), calendar time (month) to account for autonomous time trends, patient characteristics (i.e., patients’ age, sex, NIHSS score at arrival, location of the proximal intracranial occlusion, and onset-to-door time) [40], and a random effect for the hospital. This model enables us to estimate the variance of the outcome of interest (door-to-groin time) at the hospital level (inter-cluster variation) and individual level (intra-cluster variation), which in turn enables us to estimate the total effect of the performance feedback intervention. The increase in the variance due to the clustering will be quantified by the variance inflation factor. In sensitivity analyses, we will estimate the impact of the duration of exposure to the performance feedback intervention, the effect of moving from control to the intervention condition, and/or interaction of both factors on the primary outcome [41].

Multivariable normal models will be used for imputation of missing values, using available data on patient characteristics, structure, and care processes.

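### The primary model's closed covariate list omits transfer status, forgoing some precision and leaving chance or crossover-linked imbalance in transfer mix unadjusted

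*Protocol article*

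**What the plan says.** Under Study outcomes the article states: "The primary outcome is door-to-groin time". Under Indicator measurement for the dashboard it defines this as arrival to "initiation of EVT (door-to-groin time) for all patients", so transferred and direct patients are pooled. Door-to-needle time, by contrast, is confined to non-transferred patients.

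Transfer status is available for each patient. Table 1 defines the relevant structure indicator as "Whether patient transferred from another hospital to an EVT hospital", and the text adds: "We stratified the indicators by whether patients are transferred or non-transferred from another hospital".

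Statistical methods describes the primary analysis as a patient-level mixed model. It has fixed effects for intervention, for "calendar time (month) to account for autonomous time trends" and for patient characteristics, plus "a random effect for the hospital". The patient characteristics are introduced by i.e. and are "age, sex, NIHSS score at arrival, location of the proximal intracranial occlusion, and onset-to-door time". Structure data are mentioned in that section only as an input to imputation.

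**The concern.** A patient who arrives by transfer may have had part of the work-up elsewhere, so time from the door to groin puncture may differ between the two routes. The article treats the route as worth separating when it reports this indicator to hospitals, but the model that estimates the trial's effect does not use it.

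Two things are at stake. First, any variation in door-to-groin time explained by transfer stays in the residual and widens the confidence interval. Second, with only 13 hospitals ordered by lottery, the transfer mix in control and intervention periods can differ by chance, or could change when a hospital crosses over. In either case a change in case mix would be counted as a change in speed of care.

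Onset-to-door time is only a partial substitute. It runs from onset (or last seen well) to arrival at the intervention hospital, so a late-presenting direct patient and a transferred patient can have the same value.

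**Working it through.** **Inputs from the article (Power calculation, Trial design).** SD 47 min, ICC 0.37, target reduction 10 min, 5% significance (taken as two-sided), 30 patients per centre per 3 months, steps every 6 months, 13 hospitals as "three clusters of three hospitals and one cluster of four hospitals", hence five periods.

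**Variance components.** Between hospitals: 0.37 × 47² = 817 min². Within hospitals: 0.63 × 47² = 1392 min².

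**Reproducing the stated power.** The Hussey-Hughes variance is

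Var = I·s²(s² + T·τ²) / [(I·U − W)s² + (U² + I·T·U − T·W − I·V)τ²],

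where I is the number of hospitals, T the number of periods, s² = 1392/m and m the patients per hospital-period. U is the number of intervention cells; W and V are the sums of squared period totals and squared hospital totals of those cells.

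- 12 hospitals (3 per step), m = 30: U = 30, W = 270, V = 90. SE = 3.20 min, power 87.8%, which matches the stated 88%.
- 13 hospitals (3, 3, 3, 4), m = 30: U = 31, W = 295, V = 91. SE = 3.07 min, power 90.3%.
- 13 hospitals, m = 60 (a 6-month step at the stated rate): SE = 2.17 min, power 99.6%.

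No transfer covariate enters any of these, so the 88% does not depend on this point.

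**Precision.** The transfer share p and the gap d between direct and transferred patients are not in the article, so both are assumed. The fraction of within-hospital variance explained is R² = p(1 − p)d²/1392, and the SE is multiplied by about √(1 − R²). Each cell shows R², then the fall in SE.

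| Gap d | p = 30% | p = 50% | p = 60% |
|---|---|---|---|
| 10 min | 1.5%, 0.8% | 1.8%, 0.9% | 1.7%, 0.9% |
| 20 min | 6.0%, 3.1% | 7.2%, 3.7% | 6.9%, 3.5% |
| 30 min | 13.6%, 7.0% | 16.2%, 8.4% | 15.5%, 8.1% |
| 40 min | 24.1%, 12.9% | 28.7%, 15.6% | 27.6%, 14.9% |

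With 13 hospitals and m = 30, power would rise from 90.3% to about 90.8% (d = 10), 92% (d = 20), 94 to 94.5% (d = 30) or 96 to 97% (d = 40). With m = 60 it is already 99.6%. All these gains are upper bounds, because onset-to-door time is in the model and may carry part of the transfer effect.

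**Shifts in transfer mix.** The weights that generalised least squares gives each hospital-period under a model with period effects and a random hospital effect were applied to four patterns, for d = 10 to 40 min:

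1. A shift common to all hospitals: bias zero, absorbed by calendar time.
2. Stable differences between hospitals (SD 15 points): mean bias about 0, SD below 0.06 min, absorbed by the hospital effect.
3. Shifts in single hospitals unrelated to crossover (4 hospitals, +20 points from a random period, 2,000 random allocations): mean about 0, SD 0.2 to 0.8 min. In 95% of allocations the displacement stayed below 0.4 to 1.6 min. At the upper end (0.84 min) the total spread becomes √(3.07² + 0.84²) = 3.18 min for m = 30, or √(2.17² + 0.84²) = 2.33 min for m = 60, which is about 4% or 7% wider.
4. A shift coinciding with crossover in every hospital: bias = shift × d. Five points give 0.5 to 2 min; ten points give 1 to 4 min.

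**The case against.** A reader might infer that any change in referral patterns over the 30 months would bias the result. The design does not allow that reading. Crossover order is random, hospitals do not know their crossover date in advance, and the model has month and hospital effects. Patterns 1 to 3 above therefore give no systematic bias, only some added noise in the third. This part of the objection stands in full.

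A reader might also take transfer to be a strong determinant of door-to-groin time. The article reports no times by transfer status and no transfer share. A stratified display does not show how large a difference is, and confining door-to-needle time to direct patients concerns another outcome. The gain could be trivial.

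Nor is there a contradiction within the article. The stratification describes dashboard reporting, and the model's five covariates are the same baseline characteristics that the article uses to adjust hospital outcomes. The choice is consistent with that set but can be improved. The set is motivated there by its association with patient outcome, and no rationale specific to an in-hospital process time is given.

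On a crossover-linked change, nothing in the article suggests that one is expected. A route for it does exist: the number of transferred patients is itself a dashboard indicator, and improvement teams may set targets on indicators from crossover onward. That shows the change is possible, not that it is likely.

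**Conclusion.** The point holds in limited form. The article fixes a covariate list that leaves out a recorded variable, known at arrival, by which it splits the primary indicator elsewhere. Because the list is closed, this is not a detail left open for an analysis plan.

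The cost is a loss of precision of at most about 1 to 16% in the SE, under assumed gaps of 10 to 40 min and shares of 30 to 60%, and less after onset-to-door time. In addition, chance imbalance across 13 hospitals stays unadjusted, with an added SD of roughly 0.2 to 0.8 min in the scenario examined. Bias of 1 to 4 min against the 10 min target arises only if a 10-point change in transfer mix coincides with crossover. Neither the validity of the primary comparison nor the stated 88% power is undermined.

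**What to change.** Add transfer status (transferred versus direct) to the fixed effects of the primary model, and name it in the covariate list before the data are analysed. The variable is already collected, so the cost is one line of protocol or analysis-plan text and one parameter. Fixing it in advance also avoids a later choice between adjusted and unadjusted results.

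An intervention-by-transfer interaction, with effects reported separately for the two groups, may be added as a secondary analysis. It is optional, since the pooled effect is a valid target without it.

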### Objectives

Since stroke logistics and time metrics vary considerably between centers and within centers, and are strongly associated with outcome [21], this study aims to assess the extent to which performance feedback to healthcare providers in individual hospitals providing EVT for ischemic stroke, resulting in action plans and targets based on this feedback, reduces time from arrival at the hospital to initiation of EVT and thereby improves the quality of care.

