The (design of the) current study has some limitations. First, given that our intervention is multifaceted, it may be difficult to disentangle the relative impact of the different aspects of the intervention. However, an intervention with a combination of different strategies is more effective than approaches using a single intervention [44]. Second, the quality improvement policies of hospitals in the control phase are heterogeneous and this may influence the effect of our intervention. To facilitate the interpretation of our results, we will use semi-annual questionnaires to obtain insight into the quality improvement policies of the hospitals in the control arm. Third, outcome assessment is not blinded in our trial. However, the primary outcome (door-to-groin time) is an objective measure and therefore unlikely to bias the trial results. The assessment of the secondary outcomes NIHSS at 24 h and mRS at 3 months is not blinded as well, but because these outcomes are routinely collected through a structured algorithm, we expect the risk of bias to be limited.

Findings from this study will provide insight into the feasibility and effectiveness of structured performance feedback in reducing the time to treatment of patients with ischemic stroke treated with endovascular thrombectomy and, thereby, in improving patient outcomes. If the expected results are realized, the developed method for performance feedback is ready for wider implementation on a national and international level and can be adapted for use in other diseases.

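### The primary model allows no hospital-specific change over time; if hospital levels drift differently, its standard error is too small and the 5% test rejects too often

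*Protocol article*

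**What the plan says.** The Statistical methods section lists the terms of the primary model for door-to-groin time: fixed effects for intervention, calendar month and five patient characteristics, "and a random effect for the hospital". It then names two variance levels only, hospital and individual patient. The sensitivity analyses address duration of exposure, the effect of crossing over and their interaction; none alters the random part.

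The Power calculation section uses the same structure, with one ICC of "0.37, both obtained from the MR CLEAN Registry data", a "mean door-to-groin time of 77 min (standard deviation 47 min" min), and the statement that "this would result in 88% power to detect a clinically relevant reduction of door-to-groin time of 10 min".

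Three other places bear on whether hospital levels stay constant:
- The limitations in the Discussion say that "the quality improvement policies of hospitals in the control phase are heterogeneous and this may influence the effect of our intervention".
- Strategy for quality improvement lets each local team set its own targets and plans after crossover.
- Objectives says that "stroke logistics and time metrics vary considerably between centers and within centers".

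**The concern.** A single random intercept treats two patients of one hospital seen 24 months apart as being as alike as two seen in the same month. The common calendar-time effect gives every hospital the same trend. A stepped-wedge estimate draws heavily on within-hospital change between periods. If a hospital rises or falls for reasons of its own (staffing, a new angiography pathway, a local improvement project), the model treats that movement as patient-level noise that averages out over 60 patients. It does not average out, because all patients of that hospital-period share it.

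The high ICC sharpens this. The sampling error of a 60-patient hospital-period mean is about 4.8 min. If only 2% of the hospital variance moves between periods, the extra SD is already 4.0 min. At stake is the main conclusion: an apparent reduction could be drift in a few hospitals, reported with an interval that is too narrow.

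**Working it through.** **Inputs from the article.** 13 hospitals in four steps of 3, 3, 3 and 4; 5 periods of 6 months; total SD 47 min; ICC 0.37; 30 patients per hospital per 3 months, hence 60 per period; target effect 10 min; 5% level, taken as two-sided. **Assumed:** the CAC, which is the correlation between a hospital's true levels in two different periods. The article gives none.

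**Variances.** Total 47² = 2209. Hospital variance τ² = 0.37 × 2209 = 817.3. Patient variance = 0.63 × 2209 = 1391.7, so s² = 1391.7/60 = 23.19 for a period mean (SD 4.8).

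**The plan's own model (Hussey-Hughes).** With I = 13, T = 5, U = 31, W = 295 and V = 91,

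Var = I·s²(s² + Tτ²) / [(IU − W)s² + (U² + ITU − TW − IV)τ²]
= 13 × 23.19 × 4109.8 / (108 × 23.19 + 318 × 817.3) = 4.72, so SE = 2.17 min.

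This gives 99.6% power for 10 min. With 30 patients per period, SE = 3.07 and power is 90.3%. The stated 88% is reproduced (87.8%, SE 3.20) with 12 hospitals, three per step, and 30 patients per period. That mismatch is a separate matter, but it is why both patient numbers are carried below.

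**Adding drift.** Split τ² into a permanent part CAC·τ² and a hospital-by-period part g = (1 − CAC)·τ². At CAC 0.95, g = 40.9 (SD 6.4 min). The true variance of the planned estimator is the sandwich A⁻¹BA⁻¹, with A = ΣX′V⁻¹X and B = ΣX′V⁻¹V*V⁻¹X. Here V is the covariance that the model assumes and V* includes g. The fitted model absorbs a little of g into its residual: 1391.7 + 40.9 × 240/299 = 1424.5, which moves its SE only from 2.17 to 2.20. The true SE is 3.61.

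Type I error = 2Φ(−1.96 × model SE / true SE); at CAC 0.95 this is 2Φ(−1.96 × 2.20/3.61) = 23%.

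**60 per period, ICC 0.37**

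| CAC | hospital-period SD (min) | model SE | true SE | type I, analytic | type I, simulated |
|---|---|---|---|---|---|
| 1.00 | 0 | 2.17 | 2.17 | 5% | 5.0% |
| 0.99 | 2.9 | 2.18 | 2.53 | 9% | not run |
| 0.98 | 4.0 | 2.18 | 2.84 | 13% | 13.5% |
| 0.95 | 6.4 | 2.20 | 3.61 | 23% | 22% |
| 0.90 | 9.0 | 2.22 | 4.61 | 34% | 34% |
| 0.80 | 12.8 | 2.27 | 6.15 | 47% | 45% |

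The simulations used 2000 null trials per row, each fitted by REML with a hospital intercept and categorical month. Linear month gave similar results (22%, 31% and 49% at CAC 0.95, 0.90 and 0.80).

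**Less demanding inputs**
- 30 per period, ICC 0.37: about 5%, 7%, 9%, 15%, 23% and 33% at the six CAC values.
- 60 per period, ICC 0.10: about 9%, 13% and 19% at CAC 0.95, 0.90 and 0.80.

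**Degrees of freedom alone.** Referring the planned statistic to t on 11 df (60 per period, ICC 0.37) still gives 18%, 28% and 41% at CAC 0.95, 0.90 and 0.80.

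**After adding the hospital-by-period effect.** SE is 3.60, 4.59 and 6.06 min, and power for 10 min is 79%, 59% and 38%, at CAC 0.95, 0.90 and 0.80 with 60 per period. With 30 per period, power is 67%, 51% and 34%.

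**The case against.** The planned model is a standard one and matches the method behind the sample size, so the article is consistent with itself. If hospital deviations really are constant, the test holds its 5% level. Four further points deserve a fair hearing.

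- A reader might infer that the standard error is too small in any case, or that the true error rate is 20–45%. The article does not support that. Those figures belong to CAC between about 0.95 and 0.80, with ICC 0.37 and 60 patients per period. Nothing in the article fixes the CAC.
- A reader might infer that the protocol contradicts its own model. It does not. The variation within centers named in Objectives may be between patients, which the residual covers. The policy differences named in the Discussion may be stable, which the intercept absorbs. Together with the hospital-specific plans, these passages make unequal drift plausible; they do not state it.
- The ICC of 0.37 may be unadjusted for case mix, while the model adjusts for five characteristics. A lower adjusted ICC would shrink the inflation, as the ICC 0.10 figures show.
- The absence of a small-sample correction is no defect here. That detail commonly sits in the statistical analysis plan, which is not at hand, and the uncorrected test held 5.0% at CAC 1.00.

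All of this limits the size of the problem. It does not remove it: the article fixes the random part, offers no analysis that relaxes it, and any unequal drift of this kind pushes the error rate upwards.

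**Conclusion.** The point holds as a conditional one. The primary model rests on constant hospital deviations over 30 months, an assumption that the article neither justifies nor tests. If hospital levels drift differently, the nominal 5% test is anti-conservative: from 5% without drift to about 13% at CAC 0.98 and 46% at CAC 0.80 with the article's stated inputs, or about 9% and 33% with 30 patients per period. These figures assume equal hospital sizes, normal outcomes and the same correlation between any two periods. Because this is the primary analysis and the inflation is material even at high CAC, the matter should be settled before the data are analysed.

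**What to change.** Add a random hospital-by-period effect (6-month periods) to the primary model, or replace the constant correlation by one that decays with time within hospital. Report power over a range of CAC, for example 0.80 to 1.00, at the patient numbers actually expected.

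A small-sample degrees-of-freedom method for 13 hospitals can accompany this but cannot replace it. A permutation test over the randomised crossover order is an optional supporting analysis.

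The cost is one extra variance component and a change of wording; data collection and conduct are untouched. Intervals widen and realised power falls if drift exists, as shown above. If drift is absent, the added variance should be estimated near zero and little is lost.

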### Oversight and data monitoring

The trial Executive Committee consists of one Principal Investigator, one junior Study Coordinator, two researchers affiliated to DICA, three vascular neurologists, one neuro-interventionalist, one radiologist, and two trial methodologists. The Trial Steering Committee is the main decision-making body. It consists of members of the Executive Committee and all local Principal Investigators. The Steering Committee meets at least once a year.

All incoming data are reviewed by the Study Coordinator at the central trial office. All pseudo data from DASA are stored on the Erasmus MC’s secure server, which is only accessible by the Study Coordinator and Principal Investigator.

This study will be conducted in accordance with the principles of Good Clinical Practice, the Dutch Agreement on Medical Treatment Act (WGBO), and the European General Data Protection Regulation. All patients will receive the best medical treatment according to national and local guidelines and current insights. We use data collection exclusively for improving quality of care purposes. To protect patients’ privacy, the trusted third party MRDM processes the data on behalf of the healthcare providers in such a way that the Study Coordinator receives only pseudonymized patient data, meaning that personal data has been processed in such a way that they can no longer be linked to a specific person. These additional data are stored separately, and technical and organizational measures are taken to ensure that personal data can never be linked to a specific person.

This trial does focus on (performance feedback about) the treatment of acute ischemic stroke. No reason to assume that the ancillary or post-trial care varies between participating hospitals or is influenced by the intervention tested in this trial. Therefore, we do not expect this to confound the trial’s results.

